### Patient identification

The principal investigator and all co-investigators undertake to keep the identities of the persons who participate in the study confidential by assigning them a code.

This code will be used for all the eCRF and all the attached documents (reports of imaging exams, biology, etc.). It will be the only information which will make it possible to make the connection with the patient retrospectively.

The coding rule is the following: 1st letter of first name + first letter of surname and Inclusion number.

### Encoding data

The sponsor is required to encode patient data on all documents that may be in his/her possession (reports from biological analysis, etc.) that are attached to the CRF. All the documents attached to the SAE report will remain encoded.

### Encoding data

Medical coding:

The data manager is responsible for data coding including:

Medical history and AEs using the latest version of the Medical Dictionary for Regulatory Activities, MedDRA.

Before database lock, all coded terms must be validated by a person involved in the medical review.

Clinical data collection will be based on a clinical database and creating input templates similar to the CRF in compliance with protocol and applicable regulations.

The structure of the database and data entry screens will be approved by the sponsor of the study.

When the database has been declared to be complete and accurate, it will be locked and made available for data analysis.

## Statistics

### Description of planned statistical methods, including planned intermediate analysis schedule

Phase 2a:

The safety population included all subjects randomized into the study who received at least one dose of study drug. The intent-to-treat (exposed, ITT[E]) Population was defined as all subjects who met study criteria and were randomized into the study with documented evidence of having received at least one dose of randomized treatment and at least one post-baseline XAV-19 IgG SARS-CoV2 titers measurement. The Per-Protocol Population was defined as all subjects included in the ITT(E) Population excluding those who had at least one major protocol deviation.

The PK Concentration Population included all subjects who received XAV-19 at least once during the study. The PK Summary Population included subjects with an evaluable pharmacokinetic profile of XAV-19 on Day 8. Subjects were excluded if they missed the second dose of Day 5, only if second administration was planned according to protocol. The PK/PD Summary Population included subjects who met the criteria for both PP Population and PK Summary Population

The primary endpoint will be evaluated for ITTE population by a Kruskal-Wallis test between all placebo patients and all treated patients.

The pharmacokinetic analysis will be evaluated by the study of the accumulation, time-invariance, achievement of steady state, and dose-proportionality by ANOVA models with terms for subjects as a random effect and day as fixed effect.

Groups of treatment will be described according to variables in of the secondary endpoints. Categorical variables will be summarized by percent and continuous variable by means and standard error, and medians and interquartile range.

Phase 2b:

This is a double-blind, placebo controlled randomized trial with a two-sided type I error rate of 0.05.

Categorical variables will be summarized by percent and continuous variable by means and standard error, and medians and interquartile range.

Efficacy analyses

Summaries and analysis of efficacy data will be presented for the intent-to-treat (ITT) population and a Treated population (See §7.2.6).

Primary endpoint:

Proportion of patients who die, develop respiratory failure (requiring non-invasive ventilation, high-flow oxygen devices or invasive mechanical ventilation) between baseline and Day 15 will be compared using a logistic mixed model to take into account stratification factors (duration of symptoms prior to enrolment and sites).

Secondary hypotheses have been ordered according to relative importance.

The key secondary outcome, which is the proportion of patients who die, develop respiratory failure (requiring non-invasive ventilation, high-flow oxygen devices or invasive mechanical ventilation) between baseline and Day 8 and Day29 will be analysed as the primary endpoint.

Others secondary endpoint :

Quantitative endpoint will be compared using linear mixed model and qualitative data with logistic mixed model to take into account stratification factors.

Time data’s will be analyzed using survival model (Kaplan-Meier, Cox model). Fine & Gray method will be used to take into account competing risk.

Safety Analyses

The safety population is defined as all subjects randomized into the study but excluded who are ineligible at baseline or who have not had any dose of treatment.

Safety endpoints include death through Day 29 and through Day 60, SAEs and Grade 3 and 4 AEs. These events will be analyzed univariately. Time-to-event methods will be used for death. Each AE will be counted once for a given subject and graded by severity and relationship to COVID-19 or study intervention. AEs will be coded using the current version of the Medical Dictionary for Regulatory Activities (MedDRA). AEs will be presented by system organ class, duration (in days), start- and stop-date. Adverse events leading to premature discontinuation from the study intervention and serious treatment-emergent AEs will be presented either in a table or a listing.

More details will be described in the Statistical Analysis Plan.

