## Description and justification of the treatment plan

This is a phase 2 study with the aim to define the optimal XAV-19 dose to administrate to moderate COVID-19 patients, and to evaluate its safety and efficacy.

XAV-19 is a glyco-humanized polyclonal Antibody. Glyco-humanized polyclonal Antibodies have been evaluated for safety effects in kidney graft recipient volunteers at the five dose levels of 0.6, 1, 3, 6 and 8 mg/kg administered daily for 5 days. Cumulative doses have thus been 3, 5,15, 30 and 40 mg/kg.

The estimated half-life (T1/2) from pre-clinical non-human primate data is of approximately 5 days, while first assessments from human data predict a half-life reaching 11 days.

The phase 2a will be a single or double ascending dose (DAD), double-blind, placebo-controlled randomized study to select the optimal dose of XAV-19 for the phase 2b. Phase 2a will enroll 16 subjects in one of the two dose-level groups: Group 1 with dose level defined according to the neutralization titer of the XAV19 batch (first estimation being 0.5 mg/kg), Group 2 as 4 times higher than Group 1 (estimated 2.0 mg/kg).

Each subject of the Group 1 and the first two patients of Group 2 will receive two infusions of XAV-19 or placebo separated by an interval of 4 days (administrations on Day 1 and Day 5). Rest of patients from Group 2 will receive only one administration of XAV-19 on Day 1. In each of group 1 and 2, a sequential inclusion strategy will be applied: the first two patients will be randomized in a 1:1 ratio to receive either treatment or placebo, after safety analysis reviewed by the DSMC, the following 6 patients will be randomized to receive either treatment or placebo in a 5:1 ratio. Subjects will be dosed with a minimal interval of 24h (first to first administration). This 24h interval is meant to monitor possible adverse reaction to the product, such as local intolerance, allergy or cytokine release syndrome, that may occur in first hours after infusion^22^.

A predefined hold time of minimum 8 days (first to first administration) will be applied after dosing in group 1, for interim evaluation of safety by the DSMC, on which decisions for the second dose level will be based. Same design with sequential XAV-19 administrations will apply for the Group2 dosed at 2mg/kg.

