2) Assessment of the Pharmacologically Active Dose: Experience with transfusion of convalescent patient plasma (CP) indicated a benefit if containing anti-COVID-19 neutralizing antibodies at titers higher than 1/40 and given at a dose equivalent to 25 mg/Kg IgG. The neutralizing titer of XAV-19 is at least 40-fold higher than COVID-19 CP. Accordingly, infusions of 0.6 mg/Kg XAV-19 should result in similar effects in vivo as compared with 25 mg/Kg CP.

3) PK/PD information obtained from ex-vivo assessment of XAV-19. XAV-19 potency has been assessed in competition ELISA (inhibition of the COVID-19 spike protein binding to ACE-2 receptor) and tested in cytopathogenic effect assay (CPE) using SARS-CoV-2 infection of human Vero cells. Data showed an IC50 (concentration for reaching 50% of maximal signal in the test) of approx. 2.5 µg/mL of XAV-19 in ELISA and 10 µg/ml in the CPE assay. The volume of distribution of swine glyco-humanized IgG measured in primates (53 mL/kg) has a value close to that of the plasma suggesting that the XAV-19 IgGs will essentially circulate in the plasma. Considering an average plasma volume in human of 48 ml/Kg, infusions of 0.5 mg/Kg of XAV-19 will translate into 10 µg/mL plasma concentration (at Cmax). Infusions of 2 mg/Kg of XAV-19 will translate to approx. 40 µg/mL plasma concentration at Cmax. The elimination half-life of equivalent glyco-humanized antibodies was estimated in primates at 172h.

Based on these 3 datasets, **the proposed dose level for Group 2 of phase IIa, would be 2 mg/Kg infused on day 1 (or on day 1 and day 5 for some patients)**. It is meant to maintain trough levels of XAV-19 well above the threshold of 10 µg/mL (considered being a neutralizing threshold) for at least a week. This dosing (one administration of 2 mg/Kg) presents a 10 to 20-fold safety factor for the administration of XAV-19, as compared with previous experience with glyco-humanized swine IgG.

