**The bibliographical references are appended to the document.**

# Objectives and endpoints of Phase 2a

## Primary objective and endpoint

### Primary objective

The primary objectives of the study are to:

1. evaluate the Antibody titers of XAV-19 treated patients versus placebo treated patients at Day 8
2. assess the safety and tolerability of XAV-19.

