### Primary endpoint

The primary endpoints are the:

1. pharmacokinetic measurement of the antibody titer of XAV-19 measurements of all treated patients and of all patients in the placebo group at Day 8
2. tolerability and adverse events of XAV-19 between the two groups of treated patients and vs. placebo over 29 days, evaluated as:

- Occurrence of all suspected XAV-19 related adverse effects and incidence of serious adverse events
- Proportion of participants with treatment emergent adverse events leading to study drug discontinuation
- Incidence of major or bacterial or fungal infections
- Incidence of hypersensitivity reactions and infusion reactions
- White cell count, hemoglobin, platelets, creatinine, ALT, AST, on D1, D3, D5, D8, D15 and D29
- SARS-CoV-2 viral load over time (D1-D29), as collected by nasopharyngeal swab samples
- Time to RT-PCR virus negativity in nasopharyngeal swab samples

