### Statistical justification of the number of inclusions

Phase 2 a:

As it is a Phase 2 a, the number of patients was determined according to relevant publications of phase 2a. It was decided to enrol two cohorts of 8 patients (6 treated patients and 2 matching placebo in each cohort).

Phase 2 b:

Assuming a true treatment diminution in clinical failure rate of 10% for XAV-19 added to SoC therapy compared to placebo added to SoC therapy where a rate of 20% is expected, a sample size of 398 randomized participants provides at least 80% power that the primary analysis will be statistically significant at the two-sided 5% significance level.

The 20 patients of the open-label ancillary terminal study (150 mg dose of XAV-19) will not be included in the primary analysis. Their pharmacokinetic characteristics and variability will be compared to the parameters of randomized phase 2b patients taking part in the ancillary pharmacokinetics ancillary study and immunomonitoring ancillary study.

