### Expected level of statistical significance

The degree of significance is set at 5%.

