## List of expected ARs

In this protocol, the expected Adverse Event and Reactions are associated with drug under study, it placebo, and disease under study.

**Expected ARs for IMP,** infusion-related reactions may occur with antibody-related products and has been reported with other agents.

Adverse reaction as complete or incomplete flu-like symptoms, characterized by fever, headache, chills, myalgia or fatigue, hypersensitivity signs, can be observed.

According to IB, no serious adverse reaction have been observed with glyco-humanized swine IgG infusions, all serious reaction that will be observed will be considered as SUSARs.

**Expected ARs for Placebo,** only local AEs with pain, erythema, irritation are expected for placebo (NaCl solution); the amount of NaCl does not suggest systemic hydro electrolytic or blood pressure adverse effects, nor infection.

**Concerning the disease**, the most frequent expected serious adverse events are as follows:

- events related to COVID-19 infection: progression (or worsening) or complications of pneumonia, occurrence of acute respiratory distress syndrome (ARDS) that may require mechanical ventilation and/ or ECMO.

- other complications such as septic shock, cardiac arrest, myocardial infarction, respiratory failure, stroke, cardiogenic shock, ARDS, multisystemic failure syndrome (MDS), ... that may be life-threatening or fatal

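### The Phase 2a primary PK test compares pooled XAV-19 recipients with saline placebo, so it confirms that drug was given but by itself says nothing about dose or the 10 µg/mL target

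*Combined protocol and SAP*

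**What the plan says.** Protocol 1.3 describes Phase 2a as a "double-blind, placebo-controlled randomized study to select the optimal dose of XAV-19 for the phase 2b". Of the Group 2 dosing it says: "It is meant to maintain trough levels of XAV-19 well above the threshold of 10 µg/mL (considered being a neutralizing threshold) for at least a" (the sentence closes by naming a period of one week).

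The first primary objective (2.1.1) is to "evaluate the Antibody titers of XAV-19 treated patients versus placebo treated patients at Day 8". The matching endpoint (2.1.2) is the "pharmacokinetic measurement of the antibody titer of XAV-19 measurements of all treated patients and of all patients in the placebo group at Day 8". Safety and tolerability is a second primary objective. For the primary endpoint, 7.2.1 says: "The primary endpoint will be evaluated for ITTE population by a Kruskal-Wallis test between all placebo patients and all treated patients". The significance level in 7.2.3 is 5%.

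A comparison of Group 1 with Group 2 is secondary. The objective (2.2.1) places it at Day 8 and the endpoint (2.2.2) at Day 15. Section 7.2.1 names no test for it. That section does plan a dose-proportionality ANOVA, but the terms listed are subject and day, with no dose term. The SAP covers Phase 2b only (SAP 1.1), so protocol 7.2.1 is the only statistical text for Phase 2a.

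**The concern.** The endpoint is a drug concentration, and the comparator is a group that receives none of the drug. Protocol 8.3 describes the placebo as a NaCl solution. A difference between the arms is therefore built into the design. The test pools both dose levels, so it cannot separate them, and it makes no use of the 10 µg/mL target.

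What is at stake is how the primary result is read. A report that primary objective 1 was met with p = 0.003 sounds like support for the dose. The same p-value would appear whether the treated patients were well above the target or well below it.

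**Working it through.** **Inputs.** Protocol 7.2.2 gives two cohorts of 8, each with 6 treated and 2 placebo. From the randomisation steps in 7.2.7, treated = 2 × (1 + 5) = 12 and placebo = 2 × (1 + 1) = 4, so N = 16, which agrees. No power, effect size or SD is stated for Phase 2a, so there is no power figure to reproduce.

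**1. All treated quantifiable, all placebo not.** The 4 placebo values are tied at the bottom, with rank sum 4 × 2.5 = 10. The treated rank sum is 136 − 10 = 126.
- H before tie correction = 12/(16 × 17) × (126²/12 + 10²/4) − 3 × 17 = 8.471.
- Tie correction = 1 − (4³ − 4)/(16³ − 16) = 1 − 60/4080 = 0.9853.
- H = 8.471/0.9853 = 8.60, p = 0.0034 on 1 df. The exact permutation value is 2/C(16,4) = 2/1820 = 0.0011.

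Only ranks enter, so any set of concentrations that separates the groups gives this same result.

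**2. Some treated patients also unquantifiable (tied with placebo).**

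| Treated unquantifiable | p |
|---|---|
| 0 of 12 | 0.0034 |
| 1 of 12 | 0.0068 |
| 2 of 12 | 0.0128 |
| 3 of 12 | 0.0227 |
| 4 of 12 | 0.0382 |
| 5 of 12 | 0.0614 |

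**3. Does the result respond to dose or target?** This was simulated with the Day 8 median of 20.3 µg/mL after a single 2 mg/kg infusion (protocol 1.3), that is 20.3/2 = 10.15 µg/mL per mg/kg. Assumed, and not in the documents: lognormal variation with CV 30% to 100%, a quantification limit of 0.1 to 1 µg/mL, and second infusions ignored.
- At the planned doses the rejection rate was 100% for every CV and limit tried.
- With the lower dose at 0.5 mg/kg, CV 60% and limit 1 µg/mL, it was 100% whether the true Group 2 to Group 1 ratio was 1, 1.5, 2 or 4.
- With both doses cut 2.5-fold, purely to show how the test behaves, the Day 8 medians would be 10.15 × 0.2 = 2.0 and 10.15 × 0.8 = 8.1 µg/mL. Both are below 10 µg/mL, yet the rejection rate was 99.8% to 100%.
- The test does lose power once levels approach the quantification limit. With both doses cut 10-fold and a 1 µg/mL limit, the rejection rate was 0.1% to 14%. It responds to detectability, not to the target.

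**4. What the pooled group contains.** By Day 8 it holds 6 patients given 0.5 mg/kg twice, 1 given 2 mg/kg twice and 5 given 2 mg/kg once (protocol 1.3 and 4.1.2). Twice-dosed patients are sampled 8 − 5 = 3 days after their last infusion, single-dose patients 8 − 1 = 7 days after.

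**5. What a by-dose summary can deliver.** The exact two-sided 95% lower limit when all n patients reach the target is 0.025^(1/n): 54% for 6/6 and 48% for 5/5. For a geometric mean ratio with 6 patients per dose, the 95% CI is the estimate multiplied and divided by 1.46, 2.04 or 2.92 at CV 30%, 60% or 100%.

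**The case against.** The strongest reply is that nothing was decided on this p-value. Protocol 1.3 (Dose determination for Phase 2b) says safety and PK in both dose groups guide the choice, and it reports that 2 mg/kg was selected on that basis. Progression within Phase 2a depends on DSMC safety review. A Group 1 versus Group 2 comparison and a dose-proportionality analysis are already planned. This stands. A reader might infer that Phase 2a as a whole could not inform the dose, and the documents do not support that.

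A reader might also infer that the 5% error rate is inflated to nearly 100%. It is not. The null hypothesis is equal XAV-19 levels, which is false whenever drug is given, so near-certain rejection is power. Nor do the documents present the test as evidence of antiviral effect.

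The assay is a fair reservation. The endpoint is called a PK measurement and is kept apart from the Spike/ACE2 neutralising titre, which implies specificity to XAV-19. However, neither specificity nor a quantification limit is stated, and 7.2.1 also refers to SARS-CoV2 IgG titres in patients who are themselves infected. If the patients' own antibodies were detected, the separation could weaken, and the comparison would be harder still to interpret.

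Two further points stand in part. Phase 2a results are already in the documents, so any new analysis is post hoc. And 10 µg/mL is justified in different ways: as the IC50 in the cytopathogenic assay (protocol 1.3) and as twice the IC100 (SAP 1.1), while protocol 1.3 also gives 1 to 5 µg/mL as fully neutralising. It is nevertheless the target both documents use when they judge exposure.

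The planned by-dose work does not fully close the gap. Its time point differs between objective and endpoint, no test or interval is named for it, the ANOVA lists no dose term, and no analysis against 10 µg/mL is specified.

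**Conclusion.** The point holds for the test, not for Phase 2a. The only test named for the primary endpoint returns p = 0.003 under complete separation and stays significant with as few as 8 of 12 treated patients quantifiable. It carries no information on which dose is adequate or whether either reaches 10 µg/mL. The rank arithmetic rests on 12 versus 4 patients and on placebo values at zero or below quantification, hence on an assay specific to XAV-19. The simulated rates rest also on the assumed variability and quantification limits.

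The practical consequence is limited to how primary objective 1 is reported and read, since the dose choice was made on other grounds. The safety co-primary endpoint is unaffected.

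**What to change.** In protocol 7.2.1:
- Stop using the pooled treated-versus-placebo p-value as evidence for primary objective 1.
- Report by dose and regimen the Day 8 geometric mean with 95% CI, and the number of patients at or above 10 µg/mL with an exact CI. Show the twice-dosed Group 2 patient separately.
- Keep placebo samples as a check of assay specificity, and state the assay's specificity and quantification limit.
- Add a dose term to the dose-proportionality ANOVA.
- Reconcile Day 8 in 2.2.1 with Day 15 in 2.2.2 for the between-group comparison.
- Label the by-dose estimates as specified after the data were known, because Phase 2a results are already given in protocol 1.3 and SAP 1.1.

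The cost is wording and a short re-analysis. Day 8 samples are scheduled for every Phase 2a patient, so no new data are needed. The drawbacks are wide intervals, as the 54% and 48% lower limits show, and the post hoc label.

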Although data discussed above suggest that a single dose of 2 mg/kg will be sufficient to provide clinical activity and support administration of this single unique dose in the second cohort, the first two patients of this second cohort (1 XAV-19, 1 placebo) will receive 2 doses of 2 mg/kg, as initially planned, to confirm relevant PK/PD information and safety information before moving to the single high dose administration to the rest of the cohort (n = 6). It can be argued that avoiding 2 doses will diminish non necessary potential safety issues and will facilitate hospital discharge in patients with rapid recovery.

All patients will be closely monitored by a data safety monitoring committee (DSMC) during the study for emerging efficacy and overall safety data to ensure that the benefits and risks of study participation remain acceptable. Strict rules have been defined to recommend the discontinuation of XAV-19 dose at any time during the study in case of safety (Section 4.1.2.1, Dose Adjustment).

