## Secondary objectives and endpoints

### Secondary objectives

The secondary objectives of the study are:

1. To characterize pharmacokinetics (PK) of XAV-19 infected patients over the time from D1 to D29
2. To evaluate the Antibody titers of XAV-19 and to compare Group 1 treated patients versus Group 2 treated patients at Day 8.
3. To describe groups of patients according to clinical variables (Duration of supplemental oxygen, transfer in ICU, Normalization of fever, titer of Biomarkers, Ordinal scale assessed at Day 15, Hospital length of stay).

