### Secondary endpoint(s)

The secondary endpoints are the:

1. Pharmacokinetic analysis: Antibody titer measurements at Day 1 (pre-dose, post-dose), Day 3, Day 5 (if applicable second XAV-19 administration): pre-dose and post-dose), Day 8, Day 15, and Day 29.
2. The antibody titer of XAV-19 measurements in Group 1 treated patients and Group 2 treated patients at Day 15.
3. Clinical aspects:

- Duration of supplemental oxygen
- Transfer to intensive care unit with need for invasive mechanical ventilation or high flow oxygen
- Normalization of fever ≥ 24 hours: clinical assessment every day from Day 1 to Day 14. Evaluation to be performed between 8 and 12 am, Day X evaluation will consider the higher value during Day X-1 (8 am to 8 am)

- Normal fever (≤ 37.8° C tympanic or ≤ 36.6°C axillary or ≤ 37.2°C oral taken 4 hours apart from antipyretic administration) each day and time to resolution of fever for at least 48 hours

- Biomarkers : CRP, Ferritin
- Ordinal scale assessed at Day 15. The 7-point ordinal scale is an assessment of the clinical status at the first assessment on day 15. The scale is as follows:

1. Not hospitalized, no limitations on activities;
2. Not hospitalized, limitations on activities;
3. Hospitalized, not requiring supplemental oxygen;
4. Hospitalized, requiring supplemental oxygen;
5. Hospitalized, on non-invasive ventilation or high flow O2 devices;
6. Hospitalized, on invasive mechanical ventilation or ECMO;
7. Death.

- Hospital length of stay

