## Description of the population in Phase 2a

In the phase 2a, two sequential groups:

- Dose 1 XAV-19 with 0.5 mg/kg (n=6) versus Placebo (n=2)

8 patients receiving two doses of treatment (day 1, day 5) and follow-up until D29

- Dose 2 XAV-19 with 2 mg/kg (n=6) versus Placebo (n=2)

2 first patients receiving two doses of treatment (day 1, day 5) and 6 patients receiving one dose of treatment at 2mg/kg at D1 and all have follow-up until D29

16 patients will be included.

If a patient does not receive the appropriate treatment or has not been followed for 8 days then he will be replaced within the limit of 20 patients in total.

Patients will be treated once or twice in 1 week with XAV-19 (at day 1 and day 5 or only at day 1) and monitored regularly during the study period (see flow chart). Patients will be hospitalized at least from Day 1 to Day 3, if discharged before Day 5 the patient will come back for on-site visits at Day 5, Day 8, Day 15 and Day 29. Visits on Day 4, Day 6, Day 7, Day 11 and Day 13 will be done via phone calls to evaluate the clinical status, collect any adverse event and any new concomitant medications.

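### Phase 2a PK: the dose-proportionality model has no dose term, and the Group 1 versus Group 2 comparison (Day 8 in one place, Day 15 in another) compares regimens rather than dose levels

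*Combined protocol and SAP*

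**What the plan says.** **Model.** Protocol Section 7.2.1 (Phase 2a) lists accumulation, time-invariance, steady state and "dose-proportionality by ANOVA models with terms for subjects as a random effect and day as fixed effect". It mentions no dose or group term, no dose normalisation and no restriction on which samples are used. The PK Summary Population in the same section requires an evaluable profile on Day 8. It excludes a patient for missing the Day 5 infusion only if that infusion was planned, so one- and two-infusion patients are pooled.

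**Comparison day.** The Phase 2a secondary objectives (Section 2.2.1) evaluate titers and intend "to compare Group 1 treated patients versus Group 2 treated patients at Day 8". The secondary endpoints (Section 2.2.2) give a different day: "The antibody titer of XAV-19 measurements in Group 1 treated patients and Group 2 treated patients at Day 15".

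**Regimens.** Section 1.3 sets the higher dose level at four times the lower (0.5 and 2.0 mg/kg). It states: "Each subject of the Group 1 and the first two patients of Group 2 will receive two infusions of XAV-19 or placebo", on Day 1 and Day 5. It then adds: "Rest of patients from Group 2 will receive only one administration of XAV-19 on Day 1". Under the Phase 2a dose determination, "the first two patients of this second cohort (1 XAV-19, 1 placebo) will receive 2 doses of 2 mg/kg". Section 5.1 gives six active patients per group. Section 1.1 reports the same split as carried out: of six patients at 2 mg/kg, one had two doses and five had one.

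The SAP states in Section 1.1 that it covers only the second step of the study, so it adds nothing on these points.

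**The concern.** There are two separate problems, and correcting one does not correct the other.

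First, dose-proportionality asks how concentration changes between dose levels. A model that contains only subject and day has no parameter for that question.

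Second, at Day 8 or Day 15 the two groups differ in dose per infusion, number of infusions and time since the last infusion. A ratio of their titers mixes all three. Adding a dose term while keeping those days would give an estimate, but a distorted one.

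At stake is what Phase 2a can say about whether exposure scales with dose. Protocol Section 1.3 says that PK in both dosing groups guides the Phase 2b dose. Its flat-dose argument also scales Cmax linearly with mg/kg: 3 mg/kg to 75 µg/mL and 1.25 mg/kg to about 30 µg/mL, which is 25 and 24 µg/mL per mg/kg. A sound check of proportionality would support that argument. The plan as written does not supply one.

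**Working it through.** **1. Reproduce the plan's own figure.** Section 1.3 uses a plasma volume of 48 mL/kg and projects a Cmax of 10 µg/mL at 0.5 mg/kg and about 40 µg/mL at 2 mg/kg. Dose divided by volume gives 500/48 = 10.4 and 2000/48 = 41.7 µg/mL. These agree after rounding, and the ratio is exactly 4. After one infusion each, proportional kinetics mean a ratio of 4.

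**2. What the stated model can estimate.** Its parameters are an intercept, day effects and a between-subject variance. Every patient receives the same mg/kg at each infusion, so dose level is constant within subject. The difference between dose groups is absorbed into the between-subject variance. No coefficient measures it, so there is nothing to test. This step needs no PK assumption.

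**3. What a Day 8 or Day 15 ratio would show.** Assume linear one-compartment decline with half-life T days, proportional to dose, with f(t) = 2^(−t/T). Day 8 is 7 days after the first infusion and 3 days after the second. Day 15 is 14 and 10 days after.

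- Group 1 at Day 8: 0.5 × [f(7) + f(3)]
- Group 2, one infusion: 2 × f(7)
- Ratio R = 2f(7) / {0.5 × [f(7) + f(3)]} = 4 / (1 + 2^(4/T))

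The sampling day cancels, so R is the same at Day 15. The one Group 2 active patient with two infusions has a ratio of 4 to Group 1. The ratio of group arithmetic means is therefore (5R + 4)/6.

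| Half-life T (source) | 2^(4/T) | R, single-infusion Group 2 | (5R + 4)/6, all Group 2 active |
|---|---|---|---|
| 5 d (primates, Section 1.3) | 1.741 | 1.46 | 1.88 |
| 172 h = 7.17 d (primates, Section 1.3) | 1.472 | 1.62 | 2.01 |
| 11.4 d (Phase 2a median, Section 1.3; SAP Section 1.1) | 1.275 | 1.76 | 2.13 |

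At the top of the Phase 2a range in SAP Section 1.1 (13.9 d) the values are 1.80 and 2.17. Because 2^(4/T) is always above 1, R stays below 2 for any half-life.

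Relative to 4, the whole-group ratio is 53% low at T = 5 d (1 − 1.88/4) and 47% low at T = 11.4 d (1 − 2.13/4). For single-infusion patients alone the figures are about 64% and 56%.

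**4. Sensitivity to the one-compartment assumption.** The Phase 2a medians in Section 1.3 (Cmax 50.4, Day 8 20.3 µg/mL) show a faster early fall than 11.4 d implies, since 50.4 × 2^(−7/11.4) = 32.9. A bi-exponential curve was matched to both medians, with terminal half-life 11.4 d and assumed distribution half-lives of 0.5 to 2 d. It gives R = 1.57 to 1.75 at Day 8 and 1.73 to 1.76 at Day 15. The conclusion does not change.

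**5. A single-infusion comparison in the documents.** Section 1.2.1 gives preliminary Day 5 levels after one dose of around 5 µg/mL (0.5 mg/kg) and 30 µg/mL (2 mg/kg), a ratio of about 6. These are rounded values and cannot settle proportionality. They do show that the apparent direction of a departure from 4 can depend on which days are used.

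**6. Accumulation and steady state.** Five of six Group 2 active patients have one infusion and can show neither. With two infusions 4 days apart, the fraction of steady state reached is 1 − 2^(−8/T): 0.67 at T = 5 d and 0.39 at T = 11.4 d. No Phase 2a patient is planned to have more than two infusions.

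**The case against.** The strongest reply is that the plan never joins these statements. Section 7.2.1 does not tie dose-proportionality to Day 8 or Day 15, and PK samples run from Day 1 to Day 29. Sections 2.2.1 and 2.2.2 compare titers between groups without claiming to isolate the dose step. Section 7.2.1 says the groups will be described on the secondary endpoints and names no test of Group 1 against Group 2. Read as a description of two regimens, the comparison fits the stated aim of levels above 10 µg/mL for at least a week. All of this stands.

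Two stronger readings are therefore not supported:

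- A reader might infer that the planned ANOVA will make proportional kinetics look less than proportional. It will not: without a dose term it gives no proportionality estimate, biased or otherwise. The ratios above apply only if someone reads the Day 8 or Day 15 contrast as a dose comparison.
- A reader might infer that the Phase 2b dose was chosen on a distorted contrast. Section 1.3 bases that choice on safety, tolerability and PK at the higher dose, with levels set against a target concentration. The move to a single infusion rests on outside clinical data and on preliminary levels in the first low-dose patients and in four patients given a single 2 mg/kg dose. The flat-dose Cmax figures are consistent with scaling the observed Cmax at 2 mg/kg (50.4/2 = 25.2 µg/mL per mg/kg). None of these uses a between-group ratio at Day 8 or Day 15.

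It is also fair that this is a 16-patient, largely descriptive phase whose results are already reported. That limits the consequence. It does not give the model a dose term, and it does not reconcile the two days.

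**Conclusion.** The point holds as two distinct defects of modest consequence.

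The absence of a dose term follows directly from the wording: the stated analysis cannot deliver the proportionality result it promises. The contradiction between Day 8 and Day 15, and the unequal number of infusions on both days, are also plain from the text.

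The size of the second defect is conditional. It assumes linear, exactly proportional, one-compartment kinetics and a reader who takes the contrast as a dose comparison. The expected whole-group ratio is then about 1.9 to 2.1 instead of 4 for half-lives of 5 to 11.4 days. For single-infusion Group 2 patients alone it is 1.46 to 1.76. These ranges describe different sets of patients and should not be merged; the written comparison covers all treated Group 2 patients.

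The documents do not show that any dose decision relied on this contrast. The risk is that the Phase 2a PK report either has no valid statement on proportionality or carries a misleading one.

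**What to change.** In Protocol Section 7.2.1 (Phase 2a):

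- Assess dose-proportionality in actively treated patients on the Day 1 post-dose, Day 3 and Day 5 samples, the last taken before any second infusion, when every patient has had one infusion. Use log-transformed concentrations in a mixed model with subject random and with day and dose level fixed. Either dose-normalise (proportionality means a between-dose ratio of 1) or fit a power model on log dose (proportionality means a slope of 1). Report the estimate with its confidence interval.
- Report Day 8 and Day 15 titers by actual regimen: 0.5 mg/kg twice, 2 mg/kg once, 2 mg/kg twice (one active patient).
- Limit accumulation to two-infusion patients and drop the steady-state claim.

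In Sections 2.2.1 and 2.2.2, give the same day for the Group 1 versus Group 2 comparison and describe it as a comparison of regimens.

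The cost is a small amount of analysis and rewording, since the samples are already in the schedule for both groups. Because Phase 2a results are already reported, the revised analysis should be labelled post hoc. With six active patients per group the estimate will be imprecise, and the report should say so. No change to dosing or sampling is implied.
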